#### Analysis of safety

2.10.5

Safety analysis will be performed on the participants who plan to receive TEA treatment or acupuncture treatment at least once. Frequency of adverse reaction between groups, which is related with TEA treatment and acupuncture treatment, will be assessed using Chi-square test, and proportion of participants between groups, who have experienced the adverse reaction at least 1 time, will be evaluated using Chi-square test.

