### Adverse events and safety

2.6

Adverse events are defined as undesirable and unintended signs, symptoms, and diseases that develop after treatments in this clinical study process and are not necessarily caused by this clinical study. If a serious adverse event (SAE) occurs during the study, the treatment of the participant is temporarily suspended in the clinical trial, and if continuous treatment is deemed to be dangerous to the participant and if the adverse event is related to the intervention, the participant's participation in the clinical trial is discontinued. We will confirm the safety of TEA treatment by measuring blood tests and biochemical tests at the screening and after the termination of acupuncture (visit 7, visit 13) for patients. We will check the red blood cell (RBC) count, total white blood cell (WBC), hemoglobin, hematocrit, differential count, erythrocyte sedimentation rate (ESR), platelet, aspartate aminotransferase (AST), alanine aminotransferase (ALT), blood urea nitrogen (BUN), creatinine level, C-reactive protein (CRP), prothrombin time (PT), partial thromboplastin time (PTT), serum sodium level, serum potassium level, and serum chloride level.

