### Blinding

2.9

This is an open-label study comparing TEA with acupuncture treatment. It was not possible to design a double-blind for both the practitioner and the participant in this study, without revealing either the TEA or the acupuncture treatment, because of the intervention characteristics and area of application of the thread embedding treatment. In addition, the 2 groups have different number of visits.

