#### Sample size

2.10.1

This clinical trial is a pilot study, and will prepare for the primary confirmation stage and basic data about prudence in the study and clinical results before the large sample size study. Hence, rather than following the separate sample counting criteria, 20 participants were selected (20% dropout rate considered) for the experimental and control groups.

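### Adverse events are defined regardless of cause (2.6), but the comparisons in 2.10.5 are worded as treatment-related reactions, so in this open-label trial attribution can shape the between-arm result

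*Protocol article*

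**What the plan says.** Section 2.6 (Adverse events and safety) takes the broad view. Adverse events include undesirable signs and symptoms and "diseases that develop after treatments in this clinical study process and are not necessarily caused by this clinical study". The same section adds a laboratory stream: "We will confirm the safety of TEA treatment by measuring blood tests and biochemical tests at the screening" and again after treatment ends.

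Section 2.10.5 (Analysis of safety) states two between-arm comparisons. The first is "Frequency of adverse reaction between groups, which is related with TEA treatment and acupuncture treatment, will be assessed using Chi-square test". The second is the "proportion of participants between groups, who have experienced the adverse reaction at least 1 time, will be evaluated using Chi-square test". The term defined in 2.6, adverse event, does not appear in 2.10.5.

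Section 2.9 (Blinding) says "This is an open-label study comparing TEA with acupuncture treatment", and adds: "In addition, the 2 groups have different number of visits". Section 2.4 gives the schedules as 6 TEA sessions and 12 acupuncture sessions. Section 2.10.1 sets the size at 20 per group with 20% dropout considered. Section 2.2 names safety, with efficacy, as something the trial will compare.

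**The concern.** The events that 2.6 defines and the events that 2.10.5 compares are not the same set. Between them lies a judgement of relatedness, made after randomisation. Nothing in the article shields that judgement from knowledge of the arm.

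In knee osteoarthritis the judgement is not trivial. A pain flare or a swollen knee may be the disease or may follow the procedure, and the two procedures are visibly different. If such events are attributed to the disease more readily in one arm, the comparison shifts by an amount that has nothing to do with how often the events occurred. The shift can go in either direction. The pilot is also meant to supply basic data for a larger trial, so a distorted contrast would be carried forward.

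**Working it through.** **Text check.** The plan has no figure of its own to reproduce on this point, because it gives no event rate. The first step is to compare the sections.

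- 2.6: events count whether or not the study caused them.
- 2.10.5, first comparison: adverse reactions, limited in words to those related to TEA or acupuncture.
- 2.10.5, second comparison: relatedness is not repeated, but the definite article points back to the reaction just named. The restricted reading is the most natural one, though not the only one possible.
- 2.9: open-label. No section mentions a blinded assessor.
- Laboratory tests in 2.6: measured values that need no attribution.

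So at least one stated comparison, and on the natural reading both, use a set filtered by causality.

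**Illustration. Only n = 20 per arm is from the protocol; all rates and attribution fractions are assumed.**

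*A difference created.* Let the same proportion p of participants in each arm have any adverse event. Let a fraction r1 of those affected in one arm, and r2 in the other, be judged to have a related event. The related proportions are p1 = p × r1 and p2 = p × r2. The chance of p < 0.05 (two-sided, normal approximation, n = 20 per arm) is

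Φ{ [ |p1 − p2| − 1.96 √(2 p̄(1 − p̄)/n) ] / √([p1(1 − p1) + p2(1 − p2)]/n) }, with p̄ = (p1 + p2)/2.

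| All-cause p, both arms | r1 v r2 | Related p1 v p2 | False difference | Chance of p < 0.05 |
|---|---|---|---|---|
| 20% | 50% v 80% | 10% v 16% | 6 points | about 8% |
| 40% | 50% v 80% | 20% v 32% | 12 points | about 14% |
| 60% | 50% v 80% | 30% v 48% | 18 points | about 21% |
| 20% | 50% v 100% | 10% v 20% | 10 points | about 14% |
| 40% | 50% v 100% | 20% v 40% | 20 points | about 28% |
| 60% | 50% v 100% | 30% v 60% | 30 points | about 48% |

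Worked line (p = 40%, 50% v 100%): p̄ = 0.30, the first root is √(2 × 0.30 × 0.70/20) = 0.145, and the second is √((0.16 + 0.24)/20) = 0.141. Then (0.20 − 1.96 × 0.145)/0.141 ≈ −0.59, and Φ(−0.59) ≈ 0.28. With no differential attribution the nominal figure would be 5%. The approximation is rough at the lowest rates.

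As counts: 12/20 v 12/20 for all events gives p = 1.00. Halving attribution in one arm gives 6/20 v 12/20, with uncorrected chi-square p = 0.057 (Fisher p = 0.111).

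*A difference hidden or enlarged.* Suppose 8/20 TEA and 4/20 acupuncture participants have an event, 40% v 20%. If half of those affected in the TEA arm are put down to the disease and none in the other arm, the comparison reads 4/20 v 4/20, 20% v 20%. If the halving falls on the acupuncture arm instead, it reads 8/20 v 2/20, 40% v 10%.

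**The case against.** The strongest reply is that this rests on loose English. Only the first comparison carries the qualifier, adverse reaction may simply stand in for adverse event, and a condensed article can leave causality procedures and full event tables to documents not shown. Part of that stands. The second comparison is ambiguous, and the absence of an attribution procedure or of further listings is no fault here. But the first comparison is not silent: it fixes the compared quantity as related reactions, and that differs from the article's own definition.

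A second reply is that a rate of related reactions is a legitimate quantity for an invasive procedure. It is, and it is worth reporting. The weakness lies in making it the stated basis of the comparison in an open-label trial.

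Some stronger readings are tempting but are not supported:

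- *That an unblinded causality call decides the safety endpoint.* No single safety endpoint is named, the laboratory tests need no such call, and the article does not say who judges relatedness. That the judgement is unblinded is inferred from the open-label design and the absence of any mention of a blinded assessor.
- *That the plan understates event rates.* A related-reaction rate is a different quantity, not a faulty estimate of the all-event rate.
- *That bruising or similar effects expected from needling would drop out.* An expected procedural effect is still related to treatment. Only attribution to the disease or another cause removes an event.
- *That comparing all events would be free of bias.* Participants and practitioners know the arm, and one arm has twice as many sessions, so reporting and detection can still differ.

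**Conclusion.** The point holds in this limited form. The adverse-event comparisons in 2.10.5 are worded on treatment-related reactions, the first explicitly and the second on its most natural reading, although 2.6 defines adverse events regardless of cause. In an open-label trial with no blinded assessor mentioned, attribution could create or hide a difference in these comparisons.

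The size cannot be derived from the documents. Under the assumed rates above, the false difference runs from 6 to 30 percentage points. These figures show what differential attribution could do; they are no evidence that it will occur. This is a pilot without a power calculation, so the harm lies mainly in the safety contrast handed to the larger trial rather than in a significance test. The change is worth making because safety is a stated aim and the correction is cheap.

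**What to change.** In 2.10.5, make the main comparison the proportion of participants in each arm with at least one adverse event as defined in 2.6, regardless of causality. Keep treatment-related reactions as a secondary, descriptive table. Use the term from 2.6 in the main comparison, so that the scope of the at-least-once proportion is no longer ambiguous.

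Add a sentence acknowledging that all-event counts remain open to reporting in an unblinded trial and to unequal contact (6 against 12 sessions). The change removes the attribution step, not those influences.

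The cost is one more table, a wording change and somewhat higher stated event rates. The definition in 2.6 already covers these events, so no extra participants or visits are needed.

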#### Randomization

2.3.3

Block randomization will be performed, the size of the block will be 4, then the experimental and control groups will be 2:2 for each block, the randomization codes will be assigned between the groups, and will be proceeded as a pilot study. Random numbers were generated by an independent statistician. Sealed opaque assignment envelopes were used for allocation concealment. Once the clinical trial starts, each participant, who meets the selection criteria, will be assigned to the experimental and control groups according the randomization code.

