### Interventions

2.4

The participants will be randomly divided into 2 groups: the experimental group and the control group. The experimental group will receive thread embedding treatment 6 times (1 time/week) in 6 weeks on 14 defined knee areas, and the control group will receive acupuncture treatments 12 times (2 times/week) in 6 weeks on 9 defined acupuncture points.

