#### Statistical analysis

2.10.2

This statistical analysis is based on “Clinical Trial Statistics Guide (KFDA, 2000)” and the statistical package used is IBM SPSS Win ver. 19.0. The last observation carried forward method is used for missing data from drop-outs. For statistical significance, the significance level is set at 5%, and ITT (intention-to-treat: intent-to-treat analysis) analysis and PP (per protocol) analysis are conducted for all data analyses. ITT analysis is applied in principle.

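### The chi-square test on the frequency of adverse reactions appears to count repeatable events as independent and names no denominator, although the arms have 6 and 12 sessions

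*Protocol article*

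**What the plan says.** Section 2.10.5 (Analysis of safety) plans two chi-square tests. The first is on reactions: "Frequency of adverse reaction between groups, which is related with TEA treatment and acupuncture treatment, will be assessed using Chi-square test". The second is on participants: "proportion of participants between groups, who have experienced the adverse reaction at least 1 time, will be evaluated using Chi-square test". Neither clause gives a denominator for the first test, and nothing is said about repeated reactions or number of sessions.

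Section 2.4 (Interventions) fixes the courses. For TEA: "The experimental group will receive thread embedding treatment 6 times (1 time/week) in 6 weeks on 14 defined knee areas". For acupuncture: "the control group will receive acupuncture treatments 12 times (2 times/week) in 6 weeks on 9 defined acupuncture points". Section 2.9 (Blinding) acknowledges that "the 2 groups have different number of visits", but only when explaining why the trial is open-label. Section 2.10.2 sets a 5% significance level.

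**The concern.** The second test already gives one yes/no value per participant. For the first to add anything, it would naturally count reactions. The second clause's reference to one or more occurrences also shows that repeats are expected. A person who reacts at one session is likely to react again, so reactions cluster within participants. Pearson's chi-square has no place for this, and its p-values are too small when the clustering is positive.

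The missing denominator is a separate gap. The answer differs according to whether reactions are set against sessions, against participants or against nothing, because one arm has twice the sessions of the other.

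The Objective section does not list safety, but the Abstract and Study design do, and the pilot is meant to inform a larger trial. A spurious safety difference could be carried into that trial.

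**Working it through.** **Inputs from the protocol.** 20 participants per arm (2.10.1), 1:1 allocation (2.3.3), 6 versus 12 sessions (2.4), 5% level (2.10.2; two-sided assumed). Planned sessions are 20 × 6 = 120 and 20 × 12 = 240. The protocol states no reaction rate and no safety power, so there is no figure of its own to reproduce.

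**Assumptions, not in the protocol.** Risk per session p of 5-20%, equal in both arms; within-participant correlation ρ of 0 to 0.3.

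**Reading A: sessions as units.** The chi-square test takes the variance of the difference in proportions as p(1−p)(1/120 + 1/240). With clustering, the variance is p(1−p)[(1+5ρ)/120 + (1+11ρ)/240]. The ratio of the second to the first is

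[2(1+5ρ) + (1+11ρ)] / 3 = 1 + 7ρ.

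The approximate true type I error is 2[1 − Φ(1.96/√(1+7ρ))], which does not depend on p. Simulation (40,000 beta-binomial trials per setting, p = 5%, 10% and 20%) agrees:

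| ρ | 1+7ρ | Formula | Simulated |
|---|---|---|---|
| 0 | 1.00 | 5.0% | 4.8% |
| 0.05 | 1.35 | 9.2% | 8.9% |
| 0.10 | 1.70 | 13.3% | 12.8-13.4% |
| 0.20 | 2.40 | 20.6% | 20.4-20.6% |
| 0.30 | 3.10 | 26.6% | 26.3-27.1% |

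**Reading B: raw counts per arm, compared 50:50.** The statistic is (X−Y)²/(X+Y), with critical value 3.84.
- Equal risk per session of 10%: expected reactions are 12 and 24, so the statistic at expectation is 12²/36 = 4.0. Simulated rejection is 51-52%. At 5% risk it is 29-40%, and at 20% risk 70-84%.
- Equal mean per participant (gamma-Poisson counts): rejection is about 5% with no overdispersion, 11% at variance inflation 1.5, 16% at 2 and 25-26% at 3. Clustering alone therefore breaks the level even with no difference per course.

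**Reading C: reactions over 20 participants.** At a mean of one reaction per participant, an arm has more than 20 reactions with probability of about 44%. The count then exceeds its denominator and no valid 2×2 table exists.

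**The participant-level test.** It has no clustering problem. With independent sessions at 5% risk, the chance of at least one reaction is 1 − 0.95⁶ = 26.5% versus 1 − 0.95¹² = 46.0%. This describes two courses of different length; it is not evidence against the event test.

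**After the change.** Computing one rate per participant (reactions/sessions) and comparing the arms by Welch t test gives a simulated type I error of 2.9-5.4% over the Reading A settings.

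**The case against.** The unit of analysis is inferred. Section 2.10.3.1 uses frequencies and percentages for categorical summaries, so the first test could mean participants per type of reaction, which has no clustering problem. That reading is possible but less natural, and it would also need to be stated. The chi-square approximation would then be weak as well: with 20 per arm the expected count is half the total, so it is below 5 whenever fewer than 10 participants in all have the reaction.

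A reader might infer that the test is shown to be invalid and that the unequal sessions bias the comparison in favour of TEA. The documents do not support that much:
- The clustering figures under Reading A use sessions as the denominator, which already handles the session difference. The exposure figures need a different denominator. One test cannot have both faults at those sizes.
- Calendar time is equal: 6 weeks of treatment and 10 weeks in all. The session schedule is part of each randomised regimen, so fewer reactions over a shorter course would be a true result per course.
- A session is not plainly a common unit of exposure. By insertions per participant the ratio is 6 × 14 = 84 to 12 × 9 = 108, not 1 to 2.
- The correlations and risks are assumed, and at zero correlation Reading A holds its level.

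All of this stands and narrows the point. It does not rescue a test whose natural reading treats repeat events as independent. An unseen analysis plan might define the unit, but the protocol itself names the test.

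**Conclusion.** The point holds in limited form. On its natural reading, the first safety test treats reactions that can repeat within a participant as independent, and it leaves its denominator open between arms with 6 and 12 sessions. With sessions as units, the nominal 5% becomes about 9% at correlation 0.05, 13% at 0.1, 20% at 0.2 and 26-27% at 0.3. With raw counts, an equal 10% risk per session gives rejection in about 52% of trials through the session difference alone. That answers a per-course question and would mislead only if read as a per-session one.

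These sizes rest on the assumed correlations and risks and on the inferred unit. The consequence is confined to one secondary safety comparison in a 40-participant pilot, and the participant-level test planned beside it is free of the repeat-event problem. The change is worth making before analysis because it is cheap.

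**What to change.** - Drop the event-level chi-square test.
- Keep the proportion of participants with at least one reaction as the main safety comparison of the two regimens as delivered. Report the risk difference with a 95% confidence interval, and use an exact test if expected counts are small.
- Report reactions descriptively, per participant and per delivered session.
- If event counts are tested, use the participant as the unit: a comparison of participant-level rates, or a Poisson model with robust standard errors, or a negative binomial model if events suffice. State whether the estimand is per course (no offset) or per session (log number of sessions as offset).

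The cost is a few lines of analysis wording and code, and somewhat wider intervals for the event comparison. Delivered sessions must be recorded for each participant; the article does not show whether this is already planned.

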**Methods and analysis::**

This study is a clinical trial to evaluate the efficacy and safety of TEA for knee osteoarthritis. Forty participants will be recruited at the hospital and after randomization into 2 groups of 20 (experimental and control); they will be treated for 6 weeks. The experimental group will receive TEA treatment 6 times (1 time/week) in 6 weeks on 14 defined knee areas, and the control group, acupuncture treatments 12 times (2 times/week) in 6 weeks on 9 defined acupuncture points. The visual analogue scale (VAS) will be used for the primary efficacy assessment and Short-form McGill Pain Questionnaire (SF-MPQ), Western Ontario and McMaster Universities Osteoarthritis Index (WOMAC) will be used for the secondary efficacy assessment. The follow-ups before clinical trial, 3 weeks after procedure, 6 weeks after procedure, and 4 weeks after the end of procedure will be done to compare the degree of pain with the control group, which received the acupuncture treatment.

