### Study design

2.2

We will conduct a single-institution, randomized controlled pilot trial to compare the efficacy and safety of TEA with acupuncture on knee osteoarthritis.

A total of 40 participants diagnosed with knee osteoarthritis will be recruited from Daegu Oriental Hospital through advertisements. The recruitment period will run from the date of Institutional Review Board (IRB) approval to December 31, 2020. The investigator will have an interview with every potential participant by telephone and schedule screening visits. During the screening visits, every potential participant will be informed in details, ample opportunities to know about all foreseeable results will be given, and written consents will be obtained from the participants. A random assignment will be performed to divide the experimental group and the control group. The probability of being assigned to the 2 groups will be the same. The experimental group will receive TEA treatment on the knee region. The control group will receive commonly used acupoints for knee osteoarthritis treatment. The visit date will be recognized 3 days before and after the visit date and carry on for 10 weeks. A flowchart of the study is illustrated in Fig. 1, and the clinical trial schedule for treatment and outcome measurement is presented in Table 1.

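### Section 2.10.5 evaluates the share of participants with an adverse reaction by a 5% chi-square test at 20 per arm; if reactions are uncommon, that test often misses a large excess and cannot support a conclusion of similar safety

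*Protocol article*

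**What the plan says.** The abstract makes safety a purpose of the trial: "This study is a clinical trial to evaluate the efficacy and safety of TEA for knee osteoarthritis". Section 2.2 (Study design) and the Discussion repeat this aim.

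For the participant-level adverse-reaction outcome, section 2.10.5 (Analysis of safety) says that the "proportion of participants between groups, who have experienced the adverse reaction at least 1 time, will be evaluated using Chi-square test". Section 2.10.2 sets the threshold: "For statistical significance, the significance level is set at 5" percent. Section 2.10.5 gives no interval, margin or bound for this comparison, and it does not say whether the chi-square is continuity-corrected.

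On size, section 2.10.1 says that, "rather than following the separate sample counting criteria", "20 participants were selected (20% dropout rate considered) for the experimental and control groups". Section 2.2 adds equal allocation: "The probability of being assigned to the 2 groups will be the same". The protocol states no adverse-reaction rate for either arm and no power for any outcome.

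**The concern.** A test of difference answers one question: are the data incompatible with equal reaction rates? In a sample this small, with few events, it will often fail to reject even when the rates differ a great deal. A p-value above 0.05 then carries little information about how much worse TEA might be.

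The pilot is meant to inform a larger trial. What that trial needs is how high the TEA reaction rate could be and how large an excess over acupuncture remains possible. A p-value gives neither. If the report follows section 2.10.5 and states only that no significant difference was found, a reader could take this as reassurance that the data do not give.

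The point concerns only the proportion of participants with at least one adverse reaction. It does not concern event counts, laboratory tests, the attribution of events to treatment or the definition of the safety set.

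**Working it through.** **Inputs from the protocol.** 20 per arm (abstract; 2.10.1), 1:1 allocation (2.2), chi-square test (2.10.5), 5% level (2.10.2). The protocol states no power or reaction rate, so there is no figure of its own to reproduce.

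**Assumption.** The acupuncture-arm risk p_A is unknown. I took values from 2.5% to 15%, with a true four-fold risk under TEA, p_T = 4 × p_A.

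**Method.** With a reactors of 20 on TEA and b of 20 on acupuncture, the miss probability is

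1 − Σ Bin(a; 20, p_T) × Bin(b; 20, p_A), summed over all tables with p ≤ 0.05.

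The Pearson statistic is X² = 40 × [a(20 − b) − b(20 − a)]² / [(a + b)(40 − a − b) × 20 × 20]. Because the version is not specified, I also ran Yates-corrected and Fisher exact tests.

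**Probability of missing a four-fold excess, 20 per arm**

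| Acupuncture v TEA | Pearson | Fisher | Yates |
|---|---|---|---|
| 2.5% v 10% | 92% | 97% | 99% |
| 5% v 20% | 71% | 83% | 90% |
| 7.5% v 30% | 54% | 67% | 71% |
| 10% v 40% | 38% | 51% | 52% |
| 15% v 60% | 13% | 20% | 23% |

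A miss of 70% or more therefore needs an acupuncture rate of about 5% or less with the plain chi-square, about 7% with Fisher and about 7.5% with Yates.

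**Sparse tables.** With equal arms, the smaller expected cell is (a + b)/2, which is below 5 whenever there are fewer than 10 reactors in total. At 5% v 20%, 98% of trials fall in that region; at 10% v 40%, 43% do. When reactions are uncommon, the named test is usually outside the range where its approximation is normally trusted.

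**What one result would show.** Take 4/20 on TEA v 1/20 on acupuncture.

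- Test: X² = 40 × (4×19 − 1×16)² / (5 × 35 × 400) = 144,000 / 70,000 = 2.06, p = 0.15.
- Estimate: difference 0.20 − 0.05 = +15 points. The Wilson limits are 0.081 to 0.416 (TEA) and 0.009 to 0.236 (acupuncture).
- Newcombe lower limit: 0.15 − √[(0.20 − 0.081)² + (0.236 − 0.05)²] = −0.07.
- Newcombe upper limit: 0.15 + √[(0.416 − 0.20)² + (0.05 − 0.009)²] = +0.37.

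The test reports no significant difference. The interval shows that an excess of up to 37 points is not ruled out. With 1/20 on acupuncture, Pearson significance needs 6/20 on TEA: X² = 40 × (6×19 − 1×14)² / (7 × 33 × 400) = 4.33, p = 0.037.

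Even 0/20 on TEA leaves an exact upper limit of 1 − 0.025^(1/20) = 16.8% (two-sided 95%).

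**The case against.** **The protocol never equates non-significance with safety.** This is correct. A reader might infer from a safety aim and a single test that p > 0.05 will be read as comparable safety, but section 2.10.5 sets no such rule. The only wording about confirming safety, in section 2.6, concerns blood and biochemical tests. What stands is narrower: the one evaluation named for this outcome could not support such a conclusion.

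**The power figure depends on an unstated rate.** This is also correct. It is tempting to say that the test misses any four-fold excess 70% of the time, or that a null result is likely however bad TEA is. Neither holds. At 15% v 60% the Pearson test misses only 13%, and at 5% v 30% (a six-fold excess) it misses 41%, so it would detect that excess more often than not.

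**Dropout would make matters worse.** One might recompute with 16 per arm, from 20 × (1 − 0.20). The safety set in section 2.10.5 rests on treatment at least once, not on completion, so 20 is the better match.

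**Low power is normal in a declared pilot, and intervals may be specified in a document not shown.** Both are fair, and neither the sample size nor the absence of an interval method is a fault by itself. The protocol does, however, commit to a particular analysis here, and that choice suits sparse data and a pilot's purpose poorly. Intervals can also be calculated later from the reported counts, so nothing is lost irretrievably; this limits the seriousness.

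**Conclusion.** The concern holds in a limited form. For the proportion of participants with at least one adverse reaction, section 2.10.5 names a large-sample test of difference at 20 per arm. If the acupuncture-arm rate is about 5% or less, the test misses a four-fold excess about 70% of the time or more, and the table will nearly always be too sparse for the chi-square approximation. At higher rates the miss falls, to 38–52% at 10% v 40% and 13–23% at 15% v 60%. All these rates are assumptions, since the protocol gives none.

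The documents do not support the claim that the trial will declare TEA safe on a non-significant p-value. They support only that the named evaluation would be no basis for doing so. This is a minor to moderate analysis and reporting improvement, not a design failure.

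**What to change.** In section 2.10.5, keep the same outcome (participants with at least one adverse reaction) and make estimation the basis of the safety statement:

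- Report the proportion in each arm with an exact (Clopper–Pearson) 95% interval.
- Report the TEA-minus-acupuncture risk difference with a 95% Newcombe interval.
- Word the conclusion by the largest excess that the interval does not rule out.
- If a test is kept, make it Fisher exact and label it descriptive.
- State that a non-significant p-value will not be presented as evidence of similar safety.

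The cost is one or two sentences and a little programming, with no added participants, visits or procedures. The downside is a less favourable safety statement, because intervals at 20 per arm will be wide.
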